### Research plan aim 2: to measure the effects of change to community-level system factors on rates of childhood obesity among Victorian children

Since HTV aims to create change at the community (LGA level) as well as the school (setting level), the proposed research plan under Aim 2 is designed to enhance understanding of how HTV has created community-level system change. It is hypothesized that:HTV changes elements of local community-level systems that influence childhood obesityDifferential changes in local community-level systems have differential effects on the LGA policy environment, school environments, child behavior and subsequent weight status

The Foresight obesity systems map [13] represents a watershed moment for systems thinking and obesity prevention as it provides the first visual representation of the complex causes of obesity. The resulting map begins with obesity at an individual level and builds to a peripheral set of 108 variables, clustered in seven domains (physiology, individual physical activity, physical activity environment, individual psychology, social psychology, food consumption and food production) that directly or indirectly influence obesity [13]. Five of these domains (individual physical activity, physical activity environment, individual psychology, social psychology and food consumption) will be incorporated into the analysis. The domains of physiology and food production have not been included at this time as the data are not readily available or are not collected at a population level. For example, physiology includes ‘level of satiety’ and level of thermogenesis’, both of which are not easily collected en masse. Similarly the food production domain contains variables which are difficult to measure such as ‘Palatability of food offerings’ and ‘Pressure for growth and profitability’.

### Study design and sampling

In order to test the stated hypothesises, data routinely collected by the Victorian Department of Health and Human Services plus other freely available data will be used to map accepted relationships between childhood obesity and its determinants as defined by the Foresight obesity systems map at the LGA level [13]. A detailed description of the study design, sampling strategy, protocols and procedures for each of these data sources are outlined in Table 2. Table 3 provides details of the available data items that will be used in the analysis of the systems influencing obesity. The data sources contain a mixture of child and adult data. While the primary interest of this study is childhood obesity, it is obesity at an LGA level not at an individual level. Data collected only from adults such as ‘Health Literacy for Healthy Eating and Physical Activity’, 'Affective attitudes (facilitators & barriers, decisional balance) for Healthy Eating and Physical Activity’, and ‘Self-efficacy for Healthy Eating and Physical Activity’ will be used to populate parameters at the LGA level as these are seen as systems indicators. Similarly adult anthropometric data will be included in the models in order to control for the influence of adult BMI on child BMI. It would be expected that there would be a medium to strong correlation even at the LGA level between these variables. How these systems indicators plus individual level behaviors impact childhood obesity will then be tested.

**Table 2 Tab2:** Detailed description of datasets to be incorporated in Aim 2

Survey	Description (Study design, sampling and study protocol)	Participants, recruitment measures and procedures	Outcome(s) of interest	Instrument/measure
Victorian Population Health Survey (VPHS) [58]	Established in 1998, the VPHS is a Victorian representative surveillance survey that collects detailed information on the health, lifestyle and wellbeing status of Victorian adults. Random digit dialling of registered telephone numbers was used in each study year (annually from 2001) with participants completing a computer assisted telephone interview (CATI). In 2008 and 2011/12, sampling occurred in all of the 79 LGAs within Victoria and represented baseline measures for HTV. A target sample of 426 interviews per LGA was achieved. Triennial LGA-level data collection among over 33,000 is envisaged for the duration of the HTV (2014 and 2017).	• 33,673 adults (≥18 years) in private dwellings recorded complete interviews between Sept 24 and Dec 16 2008 in HTC intervention and comparison communities • All residential households with land-line telephone connections were considered eligible for the study • Interviewers made up to six calls on different days of the week and times to establish contact with the household, which was controlled by a customised call algorithm • The average interview length was approximately 22 min. • The response rate was 64.9 %.	• Change in BMI score • Change in overweight and obesity prevalence • Change in fruit and vegetable intake • Change in the proportion meeting the Australian physical activity guidelines for adults [59]	Self-rated health status
				CATI (smoking, fruit and vegetable intake, alcohol consumption, levels of PA)
				Self-reported height and weight
Preventive Health Survey (PHS)	The Preventive Health Survey was undertaken in 2011/12 and is again scheduled for completion in 2016/2017. The PHS furthers the information derived from the VPHS as it is able to make comparison estimates for each intervention HTV area compared to its’ matched-control area. This is in contrast to the VPHS, which can only make estimates for intervention and comparison HTV areas combined.	• ≥9,500 adults (≥18 years) and ≥ 1800 children (5–18 years) randomly sampled from HTV intervention and comparison communities	• Change in BMI • Change in overweight and obesity prevalence • Change in the proportion of participants meeting Australia’s physical activity and sedentary behavior guidelines for children (5–12 years) [33] and young people (13–18 years) [34] • Change in the proportion of participants eating the required amount of fruit and vegetables [39]	Self-rated health status CATI (PA, SB environmental amenity, perceived barriers and facilitators to healthy eating and activity)
				Self-reported height and weight
School Activity Audits	The Healthy Together Achievement Program is currently being offered to all Victorian Primary and Secondary schools. The program began in 2011, and was developed by the Department of Education and Training and Department of Health & Human Services (Victoria). The Achievement Program is designed to support schools to become health promoting schools and aide in the attainment of state-wide benchmarks for health promotion. Through participation in the Achievement program, schools provide information on the schools’ engagement in prevention efforts.	• Primary and Secondary Schools involved in the Healthy Together Achievement Program • The schools’ Achievement Program Coordinator completes the audits via the online registration system.	• Uptake and dispersion of the Achievement Program across Victoria • Change in progression through the various stages of the Achievement Program and achievement of benchmarks among HTV and comparison communities over time.	Online School Activity audit
LGA Policy Metrics	The Victorian Department of Health & Human Services has conducted a content analysis of Municipal Public Health and Wellbeing Plans and Council Plans in relation to healthy eating and physical activity, as well as other health and wellbeing priorities, of the 79 LGAs in Victoria. Local council plans between 2009 and 2013 have been audited in line with the 4 year municipal planning cycles.	• Content analysis of municipal documents from 79 LGAs in Victoria	• Evaluation of changes in the number and type of health and wellbeing policies within HTV intervention and comparison communities	Municipal policy documents

**Table 3 Tab3:** Details of the Foresight domains [59] and variables and the items that will be used to measure them

Foresight domain	Foresight variable	Foresight description	Data collection tool	Item
Physical activity environment	Accessibility to opportunities for physical exercise	Physical accessibility (distance, safety) of opportunities for physical exercise	PHS	Perceived environmental amenity
	Ambient temperature	Average environmental temperature indoors	Not available from surveys.	Ambient temperature
			Bureau Of Meteorology (BOM)	
			http://www.bom.gov.au/products/IDV65079.shtml	
	Cost of physical exercise	Financial cost of physical recreation	Not available from surveys	
			Data available from individual LGAs	
	Dominance of motorised transport	Degree to which motorised transport dominates other ways of transport	PHS	Perceived environmental amenity
			Data available from individual LGAs	
				Combined with
				Availability of public transport
	Dominance of sedentary employment	Degree to which average citizens influence one another’s choices	Data available from individual LGAs	Employment statistics
	Opportunity for team-based activity	N/A	Not available from surveys	Register of the number of sporting clubs in each LGA
			Data available from individual LGAs	
	Opportunity for unmotorised transport	Availability of facilities/infrastructure for unmotorised transport	PHS	Perceived environmental amenity
	Perceived danger in environment	N/A	Available from the Community Indicators Victoria website by LGA	Perceptions of safety
	Reliance of labor-saving devices	Reliance on labor-saving devices for daily chores	Not available from surveys	
	Safety of unmotorised transport	Level of risk for harm by engaging in non-motorised transport	PHS	Perceived environmental amenity
	Social depreciation of labor	Degree to which manual labor is negatively valued in a given socio-cultural group	Not available from surveys	Employment demographics
			Can be inferred from the local demographics available on the Local Government websites	
	Sociocultural valuation of physical activity	Degree to which physical activity is positively valued in a given socio-cultural group	PHS	Social environment (social norms) for HEPA
	Walkability of living environment		PHS	Perceived environmental amenity
			Available from the Community Indicators Victoria website by LGA	
				School walkability
Individual physical activity	Degree of innate activity in childhood	Degree to which physical activity is part of typical childhood behavior	PHS and WHOCC surveys	Level of physical activity
	Degree of physical education	Degree to which people have learned to use their body (for labor, leisure and transport)	VPHS	Frequency and amount of vigorous physical activity in past week
			PHS	
				Physical Activity and sedentary
	Functional fitness	Level of physical fitness to perform daily tasks	VPHS	Self-reported health status
			WHOCC	
				Paediatric Quality of Life Inventory (PedsQL) [40]
	Learned activity patterns in early childhood	Degree of activity experienced by the foetus, newborn and child in early life through parental physical activity	Not available from surveys	
	Level of domestic activity	Level of physical activity exhibited in the domestic arena	VPHS	Physical activity at work
	Level of occupational activity	Level of physical activity associated to professional duties	VPHS	Physical activity at work
	Level of recreational activity	Degree to which people engage in physical activity for recreation	VPHS	Frequency and amount of vigorous physical activity in past week
			PHS	
				Physical Activity and sedentary
	Level of transport activity	Level of physical activity associated to transport	Not available from surveys	
			Available from the Community Indicators Victoria website by LGA for Melbourne metropolitan area only	
	Non-volitional activity (NEAT)	extent to which people engage in non-volitional activity (twitching etc.)	Not available from surveys	
	Parental modelling of activity	Degree to which parents act as a role model in physical activity related behavioral patterns	PHS	Parent physical activity
				Child physical activity
	Physical activity	Level of physical activity people engage in	VPHS	Frequency and amount of vigorous physical activity in past week
			PHS	
				Physical Activity and sedentary
Social psychology	Acculturation	Degree to which a (dominant) culture is assimilated	VPHS	Country of birth
				Main language spoken at home
				Country of birth of mother
				Country of birth of father
	Availability of passive entertainment options	Availability of recreational options that involve only limited physical exercise (tv, computer games)	PHS	Sedentary behavior items
	Children’s control of diet	Degree to which children exert influence on dietary choices in a family	Not available from surveys	
	Conceptualisation of obesity as a disease	Degree to which people consider obesity to be an abnormal deviation from the healthy norm	Not available from surveys	
	Education	N/A	VPHS & PHS	Demographics
	Exposure to food advertising	N/A	Not available from surveys	Level of exposure to food advertising
			Available from the literature	
	Importance of ideal body-size image	Degree to which there is a dominant image of an ideal body size in a society	Not available from surveys	
	Media availability	Availability of media across formats	Not available from surveys	Data on availability of all types of media
			The Victorian Government digital innovation review Part B: The digital readiness of Victorian citizens	
	Media consumption	Degree to which people make use of the media offerings	Not available from surveys	Data on use of all types of media
			The Victorian Government digital innovation review Part B: The digital readiness of Victorian citizens	
	Parental control	Level of control exerted by parents on children’s choices	Not available from surveys	
	Peer pressure	Degree to which average citizens influence one another’s choices	PHS	Social environment (social norms) for Healthy Eating and Physical Activity
	Perceived lack of time	By all citizens, particularly those engaged in economic activity	PHS	Instrumental beliefs (facilitators & barriers, decisional balance) for Healthy Eating and Physical Activity
	Smoking cessation	Number of people quitting smoking	VPHS	Number of people smoking from one survey to the next
	Social acceptability of fatness	N/A	VPHS & PHS	Height and weight; BMI heterogeneity between LGAs
	Sociocultural valuation of food	Degree to which food is positively valued within a given socio-cultural group	PHS	Instrumental
	TV watching	Time spent watching tv	PHS	Sedentary behavior
Individual psychology	Demand for indulgence/compensation	Strength of demand for psychological release after stress or effort	Not available from surveys	
	Desire to resolve tension	Desire to resolve psychological conflict between what people desire and what they need to stay healthy	PHS	Affective attitudes (facilitators & barriers, decisional balance) for Healthy Eating and Physical Activity
				Combined with
				Behavioral intentions (desire to change behavior) for HEPA
				And Daily vegetable consumption
				Daily fruit consumption
				Physical Activity Sedentary behavior
				beliefs (facilitators & barriers, decisional balance) for Healthy Eating and Physical Activity
	Food literacy	Degree to which people are able to assess nutritional quality and provenance	PHS	Health Literacy for Healthy Eating and Physical Activity
	Individualism	Weakness of social fabric	PHS	Social environment (social norms) for Healthy Eating and Physical Activity
			vailable from the Community Indicators Victoria website by LGA	
				Level of social support
	Perceived inconsistency of science-based messages	Degree to which there is incompatibility between scientific assessments on food related issues which (are perceived) to be similar	PHS	Health Literacy for Healthy Eating and Physical Activity
	Psychological ambivalence	Degree to which people experience a psychological conflict between what people desire (e.g., fatty, sweet foods) and the need to stay healthy	PHS	Affective attitudes (facilitators & barriers, decisional balance) for Healthy Eating and Physical Activity
	Self esteem	Sense of purpose and self-confidence of individuals	PHS	Self-efficacy for Healthy Eating and Physical Activity
	Stress	Perceived level of stress by individuals	VPHS	Psychological distress (Kessler 10 Psychological Distress Scale)
	Use of medicines	N/A	VPHS	Diabetes status
				Type of diabetes
				Age first diagnosed with diabetes
				Type of healthcare received in past year
Food consumption	Alcohol consumption	N/A	VPHS	Whether had an alcoholic drink of any kind in previous
				12 months
				Frequency of having an alcoholic drink of any kind
				Amount of standard drinks consumed when drinking
				Level of frequency of high-risk drinking
	Convenience of food offerings	The degree to which food offerings cater to the desire for convenience	PHS	Food accessibility
	Demand for convenience	Consumer demand for convenient (time/effort saving) food offerings	PHS	Instrumental beliefs (facilitators & barriers, decisional balance) for Healthy Eating and Physical Activity
	De-skilling	The degree to which individuals are not able anymore to engage independently in routine tasks for daily living (such as cooking)	VPHS	Self-reported health status
				Combined with
				Number and type of chronic diseases
	Energy-density of food offerings	Number of calories per unit food weight	VPHS	Calculated from: Daily vegetable consumption
			PHS	
				Daily fruit consumption
				Milk consumption
				Water consumption
				Consumption of sugar-sweetened soft drinks
				Daily vegetable consumption
				Daily fruit consumption
	Fibre content of Food & Drink	N/A	VPHS	Daily vegetable consumption
			PHS	
				Daily fruit consumption
				Milk consumption
				Water consumption
				Consumption of sugar-sweetened soft drinks
				Daily vegetable consumption
				Daily fruit consumption
	Food abundance	The aggregate amount of food (volume) that is at any moment in time available in UK (AU) society	Not available from surveys	The amount of food available per person in Australia
			Australian Institute of Health and Welfare 2012. Australia’s food & nutrition 2012. Cat. no. PHE 163. Canberra: AIHW.	
	Food exposure	The number of food cues individuals are confronted with on a daily basis	Not available from surveys	
			Available from the literature	
	Food variety	The number of different food products (natural and processed) available at any moment in time	Not available from surveys	Categories of the amount of food available per person in Australia
			Australian Institute of Health and Welfare 2012. Australia’s food & nutrition 2012. Cat. no. PHE 163. Canberra: AIHW.	
	Force of dietary habits	The degree to which behavioral patterns related to food intake are dictated by routine and habit	PHS	Habit strength for Healthy Eating and Physical Activity
	Nutritional quality of Food & Drink	N/A	VPHS	Daily vegetable consumption
			PHS	
				Daily fruit consumption
				Milk consumption
				Water consumption
				Consumption of sugar-sweetened soft drinks
				Daily vegetable consumption
				Daily fruit consumption
	Palatability of food offerings	N/A	Not available from surveys	
	Portion size		Not available from surveys	
	Rate of eating	Time-span devoted to consuming a meal	Not available from surveys	
	Tendency to graze	Tendency to eat outside fixed meal times	Not available from surveys	

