### Data analysis

The Foresight map will be used as a basis to model relationships within and between the domains so as to demonstrate which elements of the system are changing, the strength of these changes, the elements that are resisting change and the implications of these relationships for childhood obesity.

The outlined datasets contain >75 % of the 65 variables within five domains of the Foresight map (individual physical activity, physical activity environment, individual psychology, social psychology and food consumption) and various techniques will be used to test the hypotheses. For hypothesis 1: HTV changes elements of local community-level systems that influence childhood obesity, a series of mixed effects linear regression analyses will be used. Prior to the analyses, a confirmatory factor analysis will be utilised to reduce the data within each of the Foresight domains so a factor score is obtained. Each of the factors will then be used as the dependent variable with the independent variable being study condition (HTV or non-HTV) interacting with time adjusted for hypothesised covariates. The resulting predictions will be plotted and compared to the changes in childhood obesity from Aim 1. Positive changes in each of the domains in HTC compared to non-HTC combined with positive changes in childhood obesity over the same time period would provide support for Hypothesis 1.

For hypothesis 2: Differential changes in local community-level systems have differential effects on the LGA policy environment, school environments, child behavior and subsequent weight status, a series of multi-level (individual and LGA) structural equation models will be used. The main area of interest will be the LGA level as it is the heterogeneity at this level that is important in testing hypothesis two. The first model will test the influence of each of the domains on one another plus policies within LGAs. The second will substitute school environments as the dependent variable, the third child behavior and the fourth child weight status. Child weight status will be calculated using the self-reported data from the PHS. These data will be used as they have corresponding adult data that can be used in calculating the systems-level exposures. Sensitivity analyses will be undertaken in order to calculate the differences in child weight status between the measured and self-report groups. Depending on findings, weightings may be used to correct the difference.

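### Table 3 places the same survey measures in more than one Foresight domain, so part of any domain-to-domain association in the first hypothesis 2 model comes from item re-use

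*Protocol article*

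**What the plan says.** Under Aim 2, the article selects five of the seven Foresight domains: "Five of these domains (individual physical activity, physical activity environment, individual psychology, social psychology and food consumption) will be incorporated into the analysis". The section on study design and sampling gives the item mapping its role: "Table 3 provides details of the available data items that will be used in the analysis of the systems influencing obesity".

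The Aim 2 data analysis section says how a domain becomes a variable: "a confirmatory factor analysis will be utilised to reduce the data within each of the Foresight domains so a factor score is obtained". That step is written under hypothesis 1. For hypothesis 2 the article plans a series of multilevel structural equation models, the first described as follows: "The first model will test the influence of each of the domains on one another plus policies within LGAs". It adds: "The main area of interest will be the LGA level as it is the heterogeneity at this level that is important in testing hypothesis two".

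Table 3 lists several measures in more than one domain. The PHS social norms measure appears as "Social environment (social norms) for Healthy Eating and Physical Activity" under social psychology (peer pressure) and under individual psychology (individualism). It appears as "Social environment (social norms) for HEPA" under physical activity environment (sociocultural valuation of physical activity). Under individual psychology (desire to resolve tension), the composite includes "And Daily vegetable consumption" together with daily fruit intake, and both measures also feed three variables in the food consumption domain. The article does not mention the overlap, or any cross-loading or correlated residual to deal with it.

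**The concern.** Two scores that contain the same variable are correlated even when the constructs they stand for are unrelated. If domain scores are built separately and then regressed on one another, the shared variable sits on both sides of the equation. A within-domain factor analysis cannot detect this, because it never sees the other domain's items.

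At stake is the interpretation of the first hypothesis 2 model. A path from social psychology to individual psychology, for instance, could reflect a real influence, the re-use of the social norms measure, or both. The analysis as described gives no means of telling these apart.

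**Working it through.** **Step 1: overlap in Table 3.** Five domains give 5 × 4 / 2 = 10 pairs. Abbreviations: PAE physical activity environment, IPA individual physical activity, SP social psychology, IP individual psychology, FC food consumption. VPHS is the Victorian Population Health Survey.

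| Measure (survey) | Domains and Foresight variables | Pairs added | Matching needed |
|---|---|---|---|
| Social norms (PHS) | SP (peer pressure), IP (individualism) | SP-IP | identical label |
| Instrumental beliefs (PHS) | SP (perceived lack of time), FC (demand for convenience) | SP-FC | identical label |
| Self-reported health (VPHS) | IPA (functional fitness), FC (de-skilling) | IPA-FC | identical label |
| Daily fruit, daily vegetables (PHS in IP; VPHS and PHS in FC) | IP (desire to resolve tension), FC (energy density, fibre, nutritional quality) | IP-FC | identical label |
| Social norms (PHS) | also PAE (sociocultural valuation of physical activity) | PAE-SP, PAE-IP | HEPA expanded |
| Activity and sedentary (PHS) | IPA (three variables), IP (desire to resolve tension) | IPA-IP | near-identical label |
| Sedentary behaviour (PHS) | IPA, SP (passive entertainment, TV watching) | IPA-SP | similar label |

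Running total: 4 of 10 on identical labels, 4 + 2 = 6 with HEPA expanded, 6 + 1 = 7 with the near-identical activity label, and 7 + 1 = 8 with the sedentary label. PAE-IPA and PAE-FC share nothing on any of these readings. No pair shares more than two distinct items. A stray line on beliefs under desire to resolve tension may be a broken table cell; it is not counted, and counting it would leave the total at 8.

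**Step 2: correlation created by sharing (illustration).** Assumptions: 8 equally weighted, standardised items per score; within-domain item correlation ρ from 0 to 0.5; no true relation between the domains; s shared items that belong in truth to domain A and are also entered in domain B.

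- Cov(A,B) = s(1 + 7ρ)
- Var(A) = 8 + 56ρ
- Var(B) = 8 + ρ[(8 − s)(7 − s) + s(s − 1)]
- r = Cov / √(Var(A) × Var(B))

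Results:

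- s = 1, ρ = 0: 1/√(8 × 8) = 0.125
- s = 1, ρ = 0.5: 4.5/√(36 × 29) = 0.139
- s = 2, ρ = 0: 2/√(8 × 8) = 0.25
- s = 2, ρ = 0.5: 9/√(36 × 24) = 0.306

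The range is about 0.13 to 0.31.

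**Step 3: rejection by a simple 5% correlation test.** The article gives 26 LGAs (school and participant recruitment; also 14 + 12 in the setting section). By Fisher's transformation, z = atanh(r) × √(26 − 3), and the rejection probability is 1 − Φ(1.96 − z) + Φ(−1.96 − z).

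- r = 0.125: z = 0.603, rejection 9.3%
- r = 0.139: z = 0.672, rejection 10.3%
- r = 0.25: z = 1.225, rejection 23.2%
- r = 0.306: z = 1.517, rejection 32.9%

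Simulating the exact t-test gives 9% to 10% for one shared item and 24% to 34% for two.

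**Step 4: sensitivity to the item count.** Suppose every distinct item listed in Table 3 is used (9 in PAE, 8 in IPA, 13 in SP, 15 in IP, 16 in FC, on the loosest matching), with equal weights and otherwise independent items. Then r = s/√(k₁k₂). This runs from 1/√(13 × 16) = 0.07 (SP-FC) to 2/√(13 × 15) = 0.14 (SP-IP). With only 5 usable items per domain and two shared, it is 2/5 = 0.40. The figures in Steps 2 and 3 are thus one point within a range that depends on weights and item counts the article does not fix.

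**The case against.** **Labels are not items.** Many Table 3 entries read as survey modules. Perceived environmental amenity alone serves five variables, and a norms module covering eating and activity could supply different questions to different domains. The PHS questionnaire is not shown. This stands: it is why the count is given as 4, 6 or up to 8, and why 8 of 10 should not be quoted alone. It does not remove the four pairs with identical labels, because nothing in the article says that different questions are used.

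**Composites.** Three pairs (IPA-IP, IP-FC, IPA-FC) share items only through composite variables, desire to resolve tension and de-skilling. If the first is scored as a gap between intention and behaviour, the induced correlation could be weaker or of opposite sign. This also stands, and the equal-weight illustration does not capture it. A correlation of unknown sign that arises from scoring is still not evidence of influence.

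**The factor-score step is written for hypothesis 1.** Its use in hypothesis 2 is inferred, and a structural equation model can accommodate cross-loadings. Both points are fair, and an article may leave measurement detail to an analysis plan. But the assignment of items to domains is stated here, and it is this stated mapping that creates the overlap.

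**The test is not the planned one.** The article judges domain impact by information criteria within multilevel models, not by a 5% correlation test. The rejection rates therefore show scale only and do not predict the error rate of the planned analysis.

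**Stronger readings that a reader might infer.** One is that the domain links would be wholly artificial; the overlap creates only part of each link, and real links may exist. Another is that collinearity seriously distorts the domains' relative contributions in the other three models. At r of 0.14 to 0.31 the pairwise variance inflation is 1/(1 − 0.14²) = 1.02 to 1/(1 − 0.31²) = 1.11, which does not support that. A third is to count two survey waves as 52 independent observations and quote higher rejection rates; nothing in the article supports independence between waves of the same LGAs.

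**Conclusion.** The point holds in a bounded form. Table 3 puts the same survey measures in more than one domain: 4 of 10 pairs on identical labels, 6 with HEPA expanded, and up to 8 if the PHS activity and sedentary labels denote the same items. If domain scores are built from this mapping and then related to one another, part of each affected association comes from item re-use and cannot be separated from a real one.

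The size is uncertain. The illustration rests on equal weights, eight items per score and no true relation. It further assumes that the hypothesis 2 models use the domain scores described under hypothesis 1.

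The problem is confined to Aim 2, mainly the domain-on-domain part of one of four models. In hypothesis 1 each domain score is a separate outcome, so the overlap creates no false condition-by-time effect. It should be corrected before any domain score is built, but it does not threaten the trial's main conclusions.

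**What to change.** Before any score is built, do one of the following:

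- Assign each survey item to exactly one domain in Table 3.
- Fit the five domains in one joint measurement model, with each repeated item entered once and its second (or third) domain declared in advance as a cross-loading.

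Where a repeated label covers different questions, list the questions used in each domain, so that apparent overlap can be told from real overlap. Table 3 already has domain and item columns, so the change is to its entries, with matching wording in the Aim 2 analysis section. Under single assignment, the number of pairs linked by a common item falls to 0 of 10.

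No new data are needed. The cost is the re-mapping and the analysis wording; the downside is that some domains will have fewer indicators.
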